## Abstract

**Background:**

Pulmonary hypertension (PH) is a leading cause of death in patients with systemic sclerosis (SSc). An important component of SSc patient management is early detection and treatment of PH. Recently the threshold for the diagnosis of PH has been lowered to a mean pulmonary artery pressure (mPAP) threshold of > 20 mmHg on right heart catheterization (RHC). However, it is unknown if PH-specific therapy is beneficial in SSc patients with mildly elevated pressure (SSc-MEP, mPAP 21–24 mmHg).

**Methods:**

The SEPVADIS trial is a randomized, double-blind, placebo-controlled phase 2 trial of sildenafil in SSc-MEP patients with a target enrollment of 30 patients from two academic sites in the United States. The primary outcome is change in six-minute walk distance after 16 weeks of treatment. Secondary endpoints include change in pulmonary arterial compliance by RHC and right ventricular function by cardiac magnetic resonance imaging at 16 weeks. Echocardiography, serum N-terminal probrain natriuretic peptide, and health-related quality of life is being measured at 16 and 52 weeks.

**Discussion:**

The SEPVADIS trial will be the first randomized study of sildenafil in SSc-MEP patients. The results of this trial will be used to inform a phase 3 study to investigate the efficacy of treating patients with mild elevations in mPAP.

**Trial registration:**

ClinicalTrials.gov Identifier NCT04797286.

## Background

Pulmonary hypertension (PH) is a hemodynamic condition defined by directly measured pulmonary arterial pressures from right heart catheterization (RHC). Until recently, an individual was considered to have PH when their mean pulmonary artery pressure (mPAP) was ≥ 25 mmHg at rest. In 2018, the 6th World Symposium on Pulmonary Hypertension (WSPH) lowered the threshold for a diagnosis of PH to a mPAP > 20 mmHg on resting RHC [1]. This recommendation was based on prior data describing the normal mPAP as 14 ± 6 mmHg [2], with 20mmHg therefore representing the 95th percentile of mPAP. Additionally, multiple large epidemiological studies demonstrated that there is a continuum of risk whereby a mPAP ≥ 19 mmHg is strongly associated with worse survival [3, 4]. A meta-analysis of 8 studies comprising almost 12,000 patients found that there is a 34–78% increased risk of death in those with a mPAP of 19–24 mmHg compared to those with a normal mPAP [5].

The updated definition of PH is most relevant to populations at high-risk for pulmonary hypertension who undergo routine screening. One such group of patients are those with systemic sclerosis (SSc, also known as scleroderma), who suffer from a severe autoimmune disease characterized by exaggerated fibrosis, vasculopathy, and dysregulation of the immune system that can affect the skin and internal organs. The prevalence of mild increases in mPAP (21–24 mmHg) in SSc, hereafter referred to as SSc with mildly elevated pulmonary pressures (SSc-MEP), is 10–15% [6–9]. This prevalence is similar to the prevalence of pulmonary arterial hypertension (PAH) in SSc, a form of group 1 PH with significant morbidity and mortality, when defined using the mPAP ≥ 25 mmHg cut-off [10]. Application of evidence-based PH early detection strategies such as the DETECT algorithm led to an increase in the identification of SSc patients with a mildly increased mPAP [11]. Therefore, improved early detection strategies and the changed definition of PH may significantly increase the number of SSc patients who now have PH. Compared to SSc patients with a mPAP < 21 mmHg, SSc-MEP patients have worse exercise capacity with a lower six-minute walk distance (6MWD) and peak exercise workload, along with impaired right ventricular (RV) output reserve during exercise [8], demonstrating that SSc-MEP patients have significant functional limitations.

While epidemiologic data show increased morbidity and mortality for persons with mildly elevated pulmonary artery pressures and guidelines now support lower thresholds for establishing the diagnosis of PH, there are no approved therapies for treatment of patients with this form of PH, which may substantially impact survival and progression to more severe PH. Only one prior trial has attempted to address this patient population. The EDITA study was a randomized controlled trial (RCT) of an endothelin receptor antagonist (ERA), ambrisentan versus placebo in 38 SSc subjects who either had SSc-MEP or an exercise-induced increase in mPAP [12]. Although the primary endpoint, change in mPAP after 6 months of treatment, was not different between the groups, the ambrisentan-treated participants had an improvement in resting pulmonary vascular resistance (PVR) and cardiac index (CI) change during exercise. Change in 6MWD also favored the ambrisentan group, with a 39-meter (m) improved compared to placebo [12]. This trial demonstrated the potential for a PAH medication to improve outcomes in SSc patients with mildly elevated mPAP but was limited by the mixed nature of the cohort and the selection of their primary endpoint, since mPAP is unlikely to change significantly due to the narrow range of pressures in SSc-MEP.

The lack of data examining the utility of vasodilator therapy in the management of SSc-MEP motivated the “**S**ildenafil Versus Placebo for **E**arly **P**ulmonary **V**ascular **D**isease **I**n **S**cleroderma” (SEPVADIS) Study. This study is a RCT of sildenafil versus placebo in SSc-MEP patients to investigate the following aims: (1) To determine whether sildenafil affects the 6MWD in SSc-MEP patients at 16 weeks and 1 year; (2) To determine if sildenafil affects RV function in SSc-MEP patients at 16 weeks; (3) To determine whether sildenafil affects health-related quality of life (HRQoL) in SSc-MEP patients at 16 weeks and 1 year.

## Methods

### Design and setting

SEPVADIS is a bicentric randomized, placebo-controlled, double-masked, parallel group superiority trial that is being conducted at two academic PH and SSc referral centers in the United States: Johns Hopkins University (Baltimore, MD) and Louisiana State University Health Sciences Center (New Orleans, LA).

### Participant selection

Recruitment is occurring at each study site, drawing from patient referrals and each center’s existing SSc population. The selection criteria are displayed in Fig. 1. The main inclusion criteria are a diagnosis of SSc and a diagnosis of pre-capillary PH with a mPAP 21–24 mmHg and a pulmonary artery wedge pressure (PAWP) ≤ 15mmHg. Of note, we did not include a PVR > 3 Wood units [1], which has been supported by the latest European guidelines, which lowered the PVR threshold for PAH to > 2 Wood units [13, 14]. Exclusion criteria are listed in Fig. 1 and focus on the exclusion of participants in whom sildenafil would be contraindicated, such as severe systemic hypotension, use of nitrates [15], and sickle cell disease [16].

**Fig. 1 Fig1:**
[figure not shown]
Selection criteria. SSc = systemic sclerosis; ACR = American College of Rheumatology; EULAR = European League Against Rheumatism; RHC = right heart catheterization; mPAP = mean pulmonary artery pressure; PAWP = pulmonary artery wedge pressure; TLC = total lung capacity; ILD = interstitial lung disease; HRCT = high resolution computed tomography; VQ = ventilation-perfusion scan; CTA = chest CT angiography; 6MWT = six-minute walk test; PAH = pulmonary arterial hypertension; WHO = World Health Organization; FC = functional class; LVEF = left ventricular ejection fraction; BP = blood pressure

### Interventions

Sildenafil is a phosphodiesterase-5 (PDE-5) inhibitor that was originally FDA-approved for the treatment of erectile dysfunction, but was later investigated for PAH in the SUPER trial, in which sildenafil led to improvements in 6WMD, mPAP, and functional class [17]. In a sub-group of connective tissue disease PAH, most of whom had SSc, significant benefit was seen with sildenafil [18]. This medication is used for SSc-related Raynaud’s phenomenon and digital ulcers and has been proven to be safe in a group of SSc patients with a mPAP < 25mmHg [19]. We chose a PDE-5 inhibitor rather than an ERA due to an RCT that demonstrated improved 6MWD, RV mass, and HRQoL in PAH patients who received sildenafil compared to an ERA [20]. Additionally, in patients with SSc-PAH initial treatment with PDE-5 inhibitor monotherapy was associated with less clinical worsening compared to ERA [21].

Sildenafil is being purchased from Teva Pharmaceuticals, who are not involved in the planning or conduct of this trial. Participants are randomized to either sildenafil (20 mg) or matching placebo taken three times per day. Sildenafil and placebo tablets are being over-encapsulated by the Research Pharmacy at the Johns Hopkins University (JHU) School of Medicine Research Pharmacy. At the Research Pharmacy, capsules are being packaged into bottles with a liner, cotton, and childproof cap. One bottle of drug product is dispensed to study subjects at the baseline study visit and at the 16-week visit during the treatment phase. Subjects are asked to return bottles at the 16-week and 52-week visits to allow for tracking of adherence and medication control. Randomization to drug or placebo is done in a 1:1 fashion blocked and stratified by center. All study personnel, subjects, and the statistician are blinded for the duration of the study until the last subject completes follow-up assessments. The JHU Research Pharmacist is unblinded. In the rare event that unmasking is necessary for clinical care, the Chair of the Steering Committee will make the decision to unmask, and the treating physician will call the research pharmacy to obtain the participant’s treatment assignment. Subjects will be withdrawn from the trial if the participant withdraws consent or if the principal investigator determines that the subject should be withdrawn for safety. One specific scenario in which this could occur is if the participant has a mPAP > 25mmHg and a PAWP ≤ 15mmHg on their week 16 RHC; they would be withdrawn from the trial and given guideline-based PAH treatment.

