### Data collection and participant timeline

The participant timeline is displayed in Fig. 2. Subject retention is being addressed through the following methods: extensive contact information will be recorded for each participant and the research coordinator will call before each study visit to encourage attendance. Additionally, participants are contacted and encouraged by the research coordinator to report any serious adverse events as they occur, while any other adverse event reporting occurs at the next available study visit or scheduled phone check in. Participants are being reimbursed for their time and reasonable travel expenses necessary for their participation. Non-adherence with therapy is being minimized by emphasizing the importance of compliance with study drug treatment and performing pill counts at study visits. If a participant wishes to drop-out from the treatment phase of the study or has a serious adverse event, we will continue to follow-up with the subject for study assessments to assist with safety monitoring and to avoid the problems introduced by missing data. Any missing data that will be reported as a protocol deviation to the single IRB and any other relevant monitoring authorities.

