The secondary outcomes will be analyzed similarly using linear regression models adjusting for baseline values and for sex. Prior studies have demonstrated sex-specific differences in RV structure and function as assessed by CMR [39] and in PAC [29], though to our knowledge there are no studies examining differences in TAPSE between men and women. HRQoL measures may differ by sex as well.

We will also include longitudinal models of change from baseline over the time of the trial. Exploratory multivariate analyses will be performed incorporating all the available endpoint assessments (baseline, 4 months, and 12 months) in an ANCOVA model with active treatment/placebo status as the independent variable.

We will attempt to minimize missing data by encouraging full subject participation and follow-up even if the subject stops the study drug prematurely. If there are missing data, we will perform sensitivity analyses using the mean value obtained to replace this missing data. For subjects lost to follow-up, we will use all the information available until the end of follow-up. For dropouts, we will use the lowest value obtained to replace missing data in separate sensitivity analyses.

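### As written, participants with pre-capillary progression at week 16 leave the trial and not only study drug, so their 52-week outcomes are lost

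*Protocol article*

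**What the plan says.** **Interventions.** Withdrawal from the trial follows loss of consent or an investigator's safety decision. One scenario is spelled out: it applies "if the participant has a mPAP > 25mmHg and a PAWP ≤ 15mmHg on their week 16 RHC", and then "they would be withdrawn from the trial and given guideline-based PAH treatment". The sentence does not limit the withdrawal to study drug and provides for no later assessments.

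**Data collection and participant timeline.** A different policy is given for two named cases: "If a participant wishes to drop-out from the treatment phase of the study or has a serious adverse event", then "we will continue to follow-up with the subject for study assessments". Part of the stated reason is "to avoid the problems introduced by missing data".

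**Data analysis plan.** The intent-to-treat set is everyone randomised. Missing data are to be kept down by "encouraging full subject participation and follow-up even if the subject stops the study drug prematurely". The section adds: "We will also include longitudinal models of change from baseline over the time of the trial". For subjects lost to follow-up, "we will use all the information available until the end of follow-up". Sensitivity analyses replace missing data with a mean value and, for dropouts, with the lowest value.

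**Outcomes and Background.** 6MWD, NT-proBNP, echocardiography and quality of life are measured again at 52 weeks, to judge whether any effect lasts. One-year 6MWD belongs to aim 1 and one-year quality of life to aim 3.

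**The concern.** Elsewhere the article separates leaving treatment from leaving the trial: one section speaks of the treatment phase, another of stopping study drug. The progression rule uses neither expression. A site that follows it literally would stop capsules and visits together, and the 52-week assessments of these participants would not take place.

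Those participants are not a random subset. They are selected by a haemodynamic result measured after randomisation, which sildenafil may influence; the Interventions section reports that sildenafil improved mPAP in PAH. If the trigger is met more often in one arm, the participants left at week 52 are no longer comparable between arms. At stake are the 1-year parts of aims 1 and 3 and the durability question. The primary endpoint is not, because the triggering catheterisation belongs to the same week-16 assessment as the primary 6MWD.

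**Working it through.** **The plan's own figure.** The only stated number on loss is the allowance for dropout: 27 / (1 − 0.10) = 30 enrolled, which reproduces. The article gives no rate of week-16 progression, so whether this rule adds to that loss at week 52, and by how much, cannot be worked out. If k of 27 completers meet the trigger (k is an assumption), loss at week 52 is (3 + k)/30: 13% for k = 1, 17% for k = 2, 30% for k = 6.

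**The texts side by side.**
- Data analysis plan: follow-up is sought after any premature stop of study drug. A progressor who moves to PAH treatment has stopped study drug early, so this aim covers the case and the progression rule is inconsistent with it.
- Data collection section: its two named cases are a participant's wish to leave treatment and a serious adverse event. Progression on catheterisation is not named, so the mismatch is with its purpose and not with its letter.
- Intent-to-treat set: everyone randomised belongs to it, but progressors would have no 52-week value to contribute.

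**Illustration of size (every input below is assumed, apart from 15 per arm, which is 30 split 1:1).** Let p_P and p_S be the proportions withdrawn on placebo and sildenafil. Let D be the deficit in 52-week 6MWD of progressors against others in their arm if nothing restores it, and r the share of D that PAH treatment restores. The comparator is the as-randomised difference that would be seen if progressors were followed on PAH treatment.

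Error of the completers' difference = −(p_P − p_S) × D × (1 − r); negative means that benefit is understated.

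- Equal rates: 0 m.
- 20% versus 5% (3 versus 0.75 of 15), so p_P − p_S = 0.15:

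| D | r = 0 | r = 0.5 | r = 1 |
|---|---|---|---|
| 30 m | −4.5 m | −2.25 m | 0 |
| 60 m | −9 m | −4.5 m | 0 |
| 100 m | −15 m | −7.5 m | 0 |

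- Reversed rates give the same sizes with the opposite sign.
- One excess withdrawal in an arm of 15 shifts the difference by D/15 = 2, 4 or 6.7 m at r = 0, and by half of that at r = 0.5.

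**What a longitudinal model recovers.** Take 20% versus 5% and D = 60 m, with equal SDs and equal correlation ρ between visits. Given baseline, the coefficient on week-16 6MWD is b = ρ/(1 + ρ): 0.333, 0.412 and 0.459 for ρ = 0.5, 0.7 and 0.85. If the whole deficit is already present at week 16, the error is −9(1 − r) + 9b:

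| ρ | r = 0 | r = 0.5 | r = 1 |
|---|---|---|---|
| 0.5 | −6.0 m | −1.5 m | +3.0 m |
| 0.7 | −5.3 m | −0.8 m | +3.7 m |
| 0.85 | −4.9 m | −0.4 m | +4.1 m |

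If the deficit appears only after week 16, the model recovers nothing, and the error at r = 0 stays at −9 m. So the model may remove part of the error, none of it, or overshoot.

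**The imputation analyses.** Filling in an arm's observed mean leaves the completers' difference unchanged. Filling in the lowest value penalises the progressor, but the article does not say whether this is the participant's own lowest value or the lowest in the group. Neither measures the 52-week outcome.

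**The case against.** The best defence is that the wording is loose. The article condenses a protocol that is not shown, the schedule figure is not reproduced, and no sentence cancels the 52-week visit for these participants. Read with the Data analysis plan, the rule could mean that capsules stop, PAH treatment starts and visits go on. This cannot be excluded; if it is what is meant, the amendment is a clarification.

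A reader might infer that the rule flatly contradicts the retention policy in the Data collection section. It does not: that policy names two other cases, and this withdrawal is the investigator's decision. The inconsistency rests on the broader statement in the Data analysis plan and on the intent-to-treat set.

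A reader might also infer a known bias against sildenafil. The documents do not support that. The Background expects mPAP to change little in this population, so few or no participants may meet the trigger, and the sign is open. Even the illustrative 9 m is small beside an unadjusted standard error of 75 × √(2/13.5) ≈ 29 m for 27 completers.

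The lowest-value sensitivity analysis for dropouts already goes some way towards treating progression as a poor outcome. This stands as partial mitigation.

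Finally, walk distance on open PAH treatment does not measure the durability of sildenafil, and placebo progressors could receive a drug of the same class. This stands too, and it is why the fix includes a supporting analysis.

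Participants with mPAP above 25 mmHg but PAWP above 15 mmHg fall outside the rule. That is no gap: they do not meet the pre-capillary definition used for entry, and they stay in follow-up.

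**Conclusion.** The point holds as a modest, cheaply corrected design weakness. As written, the rule loses the 52-week 6MWD, NT-proBNP, echocardiography and quality-of-life data of week-16 pre-capillary progressors. It is inconsistent with the plan's aim of follow-up after study drug stops, with the purpose of its retention policy, and with its intent-to-treat set. The missingness depends on a post-randomisation result that treatment may affect, and the planned longitudinal models and sensitivity analyses offset this only in part.

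It would be wrong to conclude that the week-16 primary result is compromised. It would also be wrong to quote any of the metre figures as an estimate: they rest entirely on assumed rates, deficits, restoration and correlations. The documents support only that the error at week 52 may be zero or of either sign. Confidence is medium, because the phrase may have been meant as stopping study drug.

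**What to change.** For this trigger, replace withdrawal from the trial with withdrawal from study drug, and add it to the cases in the Data collection section whose assessments continue. Give guideline-based PAH treatment exactly as planned. Keep the scheduled 52-week 6MWD, NT-proBNP, echocardiography and questionnaires, and analyse these participants as randomised. Report the number per arm who meet the trigger. Add a supporting 52-week analysis that accounts for rescue PAH therapy, for example by ranking participants who met the trigger below those who did not.

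Cost: a short amendment with single-IRB approval. The 52-week visit is already in the design, though the article does not say whether funding covers it for these participants. The article describes enrolment as ongoing, so the change can still help. Downside: the 52-week data will include some participants on open PAH therapy, which may dilute the difference between arms and answers the durability question only indirectly.

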### Outcomes

The primary outcome of this trial is 6MWD measured at 16 weeks. Six-minute walk distance reflects peak oxygen consumption [22] in PAH and is associated with changes in HRQoL [23], with a minimal important difference (MID) of 33 m for PAH and 24 m for SSc-PAH [23]. The 16-week timepoint was chosen since nearly every proprietary drug for PAH has been approved based on changes in 6MWD at 3–4 months as this is considered a clinically important intermediate endpoint [17, 24–27]. Second, improvement in 6MWD in SSc-PAH patients can be seen in as few as 8 weeks in treatment-naïve patients [28]. We are following patients for one year and collecting 6MWD along with other data to assess the durability of the effect of sildenafil in SSc-MEP.

Secondary endpoints include change in pulmonary arterial compliance (PAC) and RV function by cardiac magnetic resonance imaging (CMR) and echocardiography, serum N-terminal probrain natriuretic peptide (NT-proBNP), and HRQoL at 16 weeks. Six-minute walk distance, NT-proBNP, HRQoL, and echocardiography are also obtained at 52 weeks. PAC is a measure of pulmonary arterial stiffness and a contributor to RV afterload which, due to the inverse hyperbolic relationship of PVR and PAC [29], may be modifiable early in the course of PAH. This is of significant relevance in SSc-PAH, since PAC is an independent predictor of survival [30]. Echocardiographic measures of RV function include tricuspid annular planar systolic excursion (TAPSE) [31] and speckle tracking echocardiography (STE), a quantitative measurement of regional and global contractility that is responsive to PAH treatment and correlates strongly with functional capacity and hemodynamics [32]. CMR, the gold standard for RV function assessment, is being employed to quantify RV ejection fraction and RV volumes. HRQoL is assessed using the Medical Outcomes Survey Short Form-36 (SF-36) [33] and emPHasis-10, a disease-specific tool developed specifically for PAH [34]. Testing protocols were standardized between the two enrolling sites; RHC, echocardiography, and CMR done at LSU will be interpreted centrally at Johns Hopkins.

